# UPDATE trial: investigating the effects of ultra-processed versus minimally processed diets following UK dietary guidance on health outcomes: a protocol for an 8-week community-based cross-over randomised controlled trial in people with overweight or obesity, followed by a 6-month behavioural intervention

**DOI:** 10.1136/bmjopen-2023-079027

**Published:** 2024-03-11

**Keywords:** NUTRITION & DIETETICS, Obesity, PUBLIC HEALTH, Clinical Trial

## Abstract

**Introduction:**

Obesity increases the risk of morbidity and mortality. A major driver has been the increased availability of ultra-processed food (UPF), now the main UK dietary energy source. The UK Eatwell Guide (EWG) provides public guidance for a healthy balanced diet but offers no UPF guidance. Whether a healthy diet can largely consist of UPFs is unclear. No study has assessed whether the health impact of adhering to dietary guidelines depends on food processing. Furthermore, our study will assess the impact of a 6-month behavioural support programme aimed at reducing UPF intake in people with overweight/obesity and high UPF intakes.

**Methods and analysis:**

UPDATE is a 2×2 cross-over randomised controlled trial with a 6-month behavioural intervention. Fifty-five adults aged ≥18, with overweight/obesity (≥25 to <40 kg/m^2^), and ≥50% of habitual energy intake from UPFs will receive an 8-week UPF diet and an 8-week minimally processed food (MPF) diet delivered to their home, both following EWG recommendations, in a random order, with a 4-week washout period. All food/drink will be provided. Participants will then receive 6 months of behavioural support to reduce UPF intake. The primary outcome is the difference in weight change between UPF and MPF diets from baseline to week 8. Secondary outcomes include changes in diet, waist circumference, body composition, heart rate, blood pressure, cardiometabolic risk factors, appetite regulation, sleep quality, physical activity levels, physical function/strength, well-being and aspects of behaviour change/eating behaviour at 8 weeks between UPF/MPF diets, and at 6-month follow-up. Quantitative assessment of changes in brain MRI functional resting-state connectivity between UPF/MPF diets, and qualitative analysis of the behavioural intervention for feasibility and acceptability will be undertaken.

**Ethics and dissemination:**

Sheffield Research Ethics Committee approved the trial (22/YH/0281). Peer-reviewed journals, conferences, PhD thesis and lay media will report results.

**Trial registration number:**

NCT05627570

STRENGTHS AND LIMITATIONS OF THIS STUDYThis protocol outlines the methodology for a free-living study comparing the health effects of minimally processed food and ultra-processed food (UPF) diets following EWG dietary recommendations, and the effectiveness of a 6-month behavioural support programme to reduce UPF intake.Strengths of the randomised controlled trial include the long 8-week duration of each intervention diet, and provision of all food and drink to participants’ homes to provide.Strengths of the behavioural support programme include the use of evidence-based behaviour change techniques, and qualitative and quantitative analyses using a theoretical framework.A subset of participants will undergo MRI brain scans.Limitations include the exclusion of individuals with type 2 diabetes or with dietary restrictions (eg, vegan, vegetarian, halal and kosher).

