### Objectives and hypotheses

To date, no studies have assessed whether the health impact of following dietary guidelines is dependent on food processing, nor whether providing behavioural support to UK adults living with overweight/obesity can help to reduce their UPF intake.

Therefore, this study aims to compare the health effects between MPF and UPF diets that follow the EWG recommendations, and the feasibility and acceptability of a behavioural support programme to reduce UPF intake and be more physically active.

The primary objective is to compare weight change between MPF and UPF diets following EWG recommendations (table 1). Secondary objectives are to compare changes in cardiometabolic, behavioural, mental and hormonal outcomes between MPF and UPF diets following EWG recommendations and explore the feasibility and acceptability of the behavioural support intervention.

**Table 1 T1:** UPDATE trial design based on PICOT

Population	Adults (UCLH staff) living with overweight or obesity, and with ≥50% of habitual energy intake from UPFs
Intervention	A minimally processed diet complying with UK EWG guidance
Comparator	An ultra-processed diet complying with UK EWG guidance
Outcome (primary)	Mean difference in percent weight change between intervention and comparator at 8 weeks
Timepoints	Primary outcome assessed from baseline to 8 weeks follow-up on each diet

EWG, Eatwell Guide; UCLH, University College London Hospitals; UPDATE, Investigating the effects of Ultra-Processed versus minimally processed Diets following UK dietAry guidance on healTh outcomEs; UPF, ultra-processed food.

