## Methods and analysis

### Trial design and study setting

UPDATE (Investigating the effects of Ultra-Processed versus minimally processed Diets following UK dietAry guidance on healTh outcomEs) is a single-site, community-based, 2×2 cross-over randomised controlled trial (RCT) followed by a 6-month behavioural intervention, conducted in the UK by the Centre for Obesity Research, Division of Medicine, University College London (UCL) and UCL Hospitals (UCLH). The protocol was designed according to Standard Protocol Items: Recommendations for Interventional Trials guidelines (https://www.spirit-statement.org).^29^

In summary, 55 adults aged 18 or older, living with overweight/obesity (between 25 kg/m^2^ and 40 kg/m^2^), with 50% or more of habitual energy intake from UPFs will be recruited. Participants will receive an 8-week, minimum 80% UPF diet and an 8-week, minimum 80% MPF diet, both following UK EWG macronutrient recommendations, in a random order, with a 4-week washout period. All food and drink will be provided. All participants will then receive a 6-month behavioural support programme to reduce UPF (figure 1).

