10.1136/bmjopen-2023-079027.supp3Supplementary data

Participants will complete two non-consecutive 24-hour recalls at screening. If they meet all inclusion criteria and do not meet any exclusion criteria, they will complete a further two non-consecutive 24-hour recalls at baseline to confirm a habitual dietary intake of ≥50% UPF. The mean of all four recalls will be used to determine final habitual UPF intake. After which, they will be considered eligible.

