### Behavioural intervention

The study is powered for the cross-over RCT, rather than for the behavioural support intervention. Therefore, in line with the MRC guidance for developing complex interventions,^36^ the aim of this secondary aspect of the study is to explore the feasibility and acceptability of the behavioural support intervention to reduce UPF (primary target behaviour) and increase physical activity (PA) (secondary target). Full details of the intervention development and content will be provided in a future publication focused on the behavioural support intervention. The exit interview guide is provided in online supplemental material 4. However, in brief, the intervention was developed following the steps outlined in the Behaviour Change Wheel framework for intervention development,^37^ which incorporates the ‘Capability, Opportunity, Motivation’ model for understanding behaviour (COM-B), augmented with Theoretical Domains Framework (TDF) for using behaviour change theory.^36 38^ Qualitative studies of barriers and facilitators for dietary change in healthcare workers were extensively reviewed, with findings then mapped onto the TDF, and behaviour change techniques (BCT) consistently associated with successful diet and PA change drawn from meta-analyses of RCTs.^39–41^ The intervention content combines monthly video/telephone behavioural support calls with print/online resources, based on TDF domains. Some examples of TDF domains (linked to the intervention components) are knowledge (information on what UPFs are and how to recognise them), environment (mapping of food outlets local to participant’s workplace to for quickly accessible MPF options), beliefs about consequences (information about links between UPF and health), behavioural regulation (support with goal-setting, action-planning, self-monitoring, habit) and social influence (moderated online peer support sessions). The calls will be individually tailored based to participant demographics/work patterns, responses to their baseline COM-B questionnaire, baseline levels of UPF intake and reported PA (measures of these are all described in the outcomes section) and personal barriers and motivations to change.

10.1136/bmjopen-2023-079027.supp4Supplementary data

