### Outcomes

Outcome measures will be collected at seven in-person visits. See figure 1 and online supplemental material 5 for the schedule of assessments.

10.1136/bmjopen-2023-079027.supp5Supplementary data

The primary outcome is the mean difference in percent weight change (%WC) at 8 weeks from baseline between MPF and UPF diets. This outcome is currently being used clinically in weight management clinics and used for all NHS weight management programmes. Clinically significant weight change can occur from short-term dietary interventions and directly relates to improvements in cardiometabolic risk factors (eg, blood pressure, blood glucose, glycated haemoglobin (HbA1c), lipids),^42^ physical function and quality of life.^43^ Weight is an efficient and more accurate measurement to collect than other energy balance measures, such as energy intake. The hypothesised %WC in the face of the current growing obesity pandemic would have clinically relevant impacts on halting the rate of progression of obesity prevalence and mitigating the adverse impacts of adiposity-related disease, simply through shifts in the types of processed in foods being consumed.

Secondary outcomes include changes in dietary intake, waist circumference, body composition (fat mass, fat-free mass), heart rate, blood pressure, cardiometabolic risk factors (comorbidities and blood biomarkers including liver function, lipid profile, glucose, HbA1c and C reactive protein), fasted and fed metabolomics, appetite measures (fasted and fed appetite scores, circulating gut hormones and adipocytokines), sleep, sleep quality, PA levels, physical function (walking distance, leg strength, handgrip strength), mental health, quality of life, well-being and aspects of eating behaviour between MPF and UPF diets, and after the 6-month behavioural intervention compared with the first baseline assessment. In a subset of participants, changes in brain functional resting state connectivity between MPF and UPF diets will be assessed. Further behavioural intervention secondary outcomes include understanding the experiences of UPF versus MPF diets, changes in behaviour regulation and shopping expenditure from the first baseline assessment, and barriers and facilitators to reducing UPF intake.

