#### Feasibility/acceptability and process evaluation of the behavioural intervention

Feasibility/acceptability and process evaluation will be described in full in the subsequent paper focused on the behavioural intervention. However, the main feasibility/acceptability outcome will be the percentage of intervention calls successfully delivered, as well as retention to the study. For quality control intervention calls will be recorded and coded against a checklist to ensure that target BCTs are being delivered as planned. Acceptability of the intervention content and process will be gathered in qualitative interviews. Changes in other outcomes pre and post the behavioural intervention will be explored as secondary.

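### The article claims to assess the behavioural programme's effectiveness and impact, but everyone receives it and change runs from a baseline before both provided diets, so no programme effect can be estimated

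*Protocol article*

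**What the plan says.** Two summary statements describe an evaluation of effect. The strengths and limitations box names "the effectiveness of a 6-month behavioural support programme to reduce UPF intake". The Introduction paragraph of the abstract says "our study will assess the impact of a 6-month behavioural support programme aimed at reducing UPF intake".

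The body of the article is narrower. Objectives and hypotheses gives the aim for this phase as "the feasibility and acceptability of a behavioural support programme to reduce UPF intake and be more physically active". The Behavioural intervention section repeats that aim and adds: "The study is powered for the cross-over RCT, rather than for the behavioural support intervention". The Feasibility/acceptability section makes calls delivered and retention the main outcomes, and then says: "Changes in other outcomes pre and post the behavioural intervention will be explored as secondary".

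On design, Trial design and study setting gives the programme to all participants after the second diet, and Randomisation allocates only the order of the diets. Outcomes defines the 6-month comparison as the state "after the 6-month behavioural intervention compared with the first baseline assessment". Eligibility criteria requires at least 50% of energy from UPF, using two recalls at screening and two more at baseline: "The mean of all four recalls will be used to determine final habitual UPF intake".

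**The concern.** A claim of effectiveness or impact needs an estimate of what would have happened without the programme. Here there is no concurrent control, and the two randomised groups cannot supply one because both receive the programme. The before-after change does not isolate the programme either, for two reasons.

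- **Reference time.** The first baseline precedes both feeding periods and the washout. Whatever those periods leave behind is part of the 6-month change. The Sample size section itself expects 2.7% weight loss on the MPF diet, so the plan predicts weight change before the programme starts.
- **Selection on the target behaviour.** UPF intake is the programme's primary target, and people enter because recalls, including those taken at the first baseline, showed a high value. Part of that high value is day-to-day error, which will not recur at 6 months.

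At stake is how a fall in UPF intake or weight at 6 months can be read. With effectiveness in the highlights box and no mention of the missing control among the limitations there, the article invites a causal reading that its design does not support.

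**Working it through.** **1. The only powered comparison.** Inputs from Sample size: difference 2.7%, SD 5.4%, two-sided alpha 0.05, power 0.90, paired t-test.
- Standardised difference = 2.7/5.4 = 0.5. The noncentral t distribution gives n = 44 (power 0.9000).
- With 20% dropout, 44/(1 − 0.20) = 55.

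Both planned figures reproduce. They concern the cross-over only; nothing comparable is given for the behavioural phase, as the article says.

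**2. What the 6-month contrast spans.** Inputs from Interventions and Participant timeline: 8-week diet, 4-week washout, 8-week diet, then 6 months (taken as 26 weeks), within 49 weeks per participant.
- First baseline to start of programme: 8 + 4 + 8 = 20 weeks.
- On provided diets: 8 + 8 = 16 weeks.
- First baseline to 6-month follow-up: 20 + 26 = 46 of the 49 weeks.

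So 20 of the 46 weeks come before the programme begins.

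**3. Regression to the mean in UPF share.** The article gives no population mean or variance for UPF share, so these inputs are assumptions:
- population mean 50–60% of energy
- between-person SD 10–15 points
- day-to-day SD 15–20 points, independent between recalls

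A person is selected if the mean of the two screening recalls and the mean of all four are both at least 50. The apparent fall with no programme effect is the selected group's observed baseline mean minus its true mean.

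One case can be followed by hand, using selection on the four-recall mean only (population mean 50, between-person SD 10, day-to-day SD 20):
- SD of the four-recall mean = √(10² + 20²/4) = √200 = 14.1.
- Reliability = 100/200 = 0.50.
- Mean of those at or above 50 = 50 + 14.1 × 0.798 = 61.3.
- Apparent fall = (1 − 0.50) × (61.3 − 50) = 5.6 points.

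Adding the screening requirement (by simulation) raises this to 6.4 points. If only the two baseline recalls serve as the outcome baseline, it is 3.5 points, because the screening recalls carry more of the selection. Over the whole assumed grid:

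| Baseline used for UPF intake | Apparent fall from selection alone |
|---|---|
| Two baseline recalls | 0.9–3.5 points of %energy |
| Mean of all four recalls | 1.8–6.4 points of %energy |

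A different set of assumptions (mean 45–55%, SD of the recall mean 10–15, reliability 0.50–0.85, selection on the recall mean only) gives 0.8–7.7 points. The size depends on the inputs; the direction is the same throughout. The two-recall row fits the text better: the dietary assessment section specifies two recalls per visit period, and the four-recall mean is described for eligibility.

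**The case against.** The strongest reply is that the formal aim is already right. The abstract's methods, Objectives and hypotheses, Behavioural intervention and Feasibility/acceptability all point to feasibility and acceptability. The article says this phase is not powered and attaches no hypothesis or success criterion to it. An uncontrolled single-group phase is a legitimate feasibility design, and detail is deferred to a later paper. All of this stands. It confines the fault to the summary claims and to the meaning of the stated contrast; it does not remove it, because the article does make those claims and does fix the comparator.

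Four stronger readings are tempting and are not supported:

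- *The trial will credit the 6-month change to the programme.* No passage says so. Outcomes names its comparator openly; what is missing is a label for what that contrast contains.
- *The Feasibility/acceptability and Outcomes sections contradict each other on the starting point.* The wording about change pre and post the programme is looser, but a first-baseline starting point is compatible with it. For the COM-B questionnaire, the first baseline is the only earlier measurement.
- *The weight bias can be quantified.* Assuming that half of the expected 2.7% loss persists would give 1.35%, but the article offers no retention figure, and any single value would be invented.
- *The end of the second diet should replace the first baseline for weight.* That swaps one confounder for another. Participants finishing on the MPF diet are expected to be lighter, so any regain would count against the programme. A sequence term describes the difference between orders but does not remove the average rebound.

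**Conclusion.** The concern holds in a limited form. The effectiveness and impact claims in the box and the abstract are not supported by the design and do not match the aim stated in the body. The 6-month change from first baseline is a change over the whole trial, including 20 weeks before the programme starts, 16 of them on provided diets. For UPF intake, selection adds an apparent fall of about 0.9–3.5 points of %energy (two baseline recalls) or 1.8–6.4 points (four-recall mean). These ranges rest wholly on assumed means and variances and on independent daily errors; only the sign is secure. No size can be given for weight. An uncontrolled feasibility phase is not in itself an error, and the cross-over comparison and its sample size are unaffected.

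**What to change.** 1. In the abstract and the strengths and limitations box, replace *impact* and *effectiveness* with feasibility, acceptability and uncontrolled change, to match the body. List the lack of a concurrent control as a limitation.
2. Keep the first-baseline contrast, label it change over the whole trial, and state that it is not an effect of the programme. Align the Feasibility/acceptability wording with Outcomes on the reference time.
3. For UPF intake, add a contrast from the second-baseline recalls (visit 5, reading the visits in Table 4 in order), with sequence in the model. These recalls follow the washout and were not used for eligibility.
4. For weight and clinical outcomes, change from the end of the second diet (visit 7) may be reported as an additional descriptive contrast, stating that it includes rebound after the last provided diet.

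The cost is text and slightly more analysis; the visits are already scheduled. Visit 5 may carry some effect of the first diet, which is why sequence is included. None of these contrasts identifies a programme effect, so the wording change is needed whichever are reported.

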## Introduction

Obesity is a global healthcare challenge. Nearly two-thirds of UK adults now live with overweight or obesity,^1^ increasing the risk of life-limiting disease and premature mortality.^2^ The overall annual cost of obesity in the UK is estimated at £58 billion.^3^ Of which, the National Health Service (NHS) spends over £6 billion/year on obesity-related health issues, which is expected to rise to nearly £10 billion/year by 2050.^4^

A major driver of the obesity epidemic has been the shift in the food environment with increased availability of ultra-processed food (UPF).^5–7^ Defined by NOVA (not an acronym), UPFs are industrial formulations with five or more ingredients, using extracts of original foods with preservatives, flavourings and colours.^8^ UPFs include breakfast cereals, sweets, packaged breads and ready meals. Over 50% of UK energy intake now comes from UPFs, displacing more traditional minimally processed food (MPF).^9^ In prospective cohort studies, higher UPF intakes are associated with increased risks of weight gain, overweight/obesity,^10 11^ cardiometabolic disease,^12^ gastrointestinal disorders, cancer,^13^ mental health problems,^14^ lower physical strength^15^ and all-cause mortality.^16^

The Eatwell Guide (EWG) provides the UK public with guidance for a healthy, balanced diet.^4 17 18^ The EWG focuses on macronutrients and food groups, such as choosing foods lower in saturated fat, sugar and salt, and eating five daily portions of fruit and vegetables.^18^ The EWG recommends ‘reduced fat’ or ‘lower sugar’ reformulated foods, based on European Food Safety Authority nutrition claim regulations. However, this promotes the intake of UPFs.^19^ Given their improved nutritional quality from reduced saturated fat, added sugar and/or salt, reformulated UPFs are often marketed as ‘healthy’.^20^ However, the associations between high UPF intakes and adverse health outcomes appear to independent of diet quality or diet pattern.^16^

In the only randomised trial to date examining the effect of energy-matched UPF versus MPF diets, participants gained nearly 1 kg body weight on the 2-week UPF diet, but lost nearly 1 kg on the 2-week MPF diet, with over 500kcal/day differences in energy intake.^21^ The diets were also matched for presented energy density, carbohydrate, sugar, fat, sodium and fibre content. The MPF diet also led to favourable changes in appetite-regulating gut hormones compared with the UPF diet. In epidemiological substitution modelling, replacing UPFs for MPFs leads to weight loss, whereas replacing MPFs for UPFs leads to weight gain, independent of diet pattern (by adjusting for adherence to a Mediterranean diet).^22^ However, to date, UK organisations such as the British Nutrition Foundation and the Scientific Advisory Committee on Nutrition do not recommend the inclusion of UPF in dietary guidelines. This is due to the largely observational body of evidence regarding the negative impact of ultraprocessing on health and lack of high-quality interventional evidence.^23 24^

Adopting a healthy diet requires a significant behaviour change and lifestyle modification which can be challenging for many individuals. The prevalence of obesity in the UK is also present among UK healthcare professionals (HCPs).^1 25^ Many HCPs consume an unhealthy diet,^26^ attributed to the high availability and accessibility of ready-to-eat unhealthy food and lack of healthier choices in the workplace, especially during night shifts, stress-driven eating, long working hours and staff shortages limiting the ability to take breaks.^27^ It is, therefore, important to support individuals to reduce their UPF intake, and in the process, identifying barriers and facilitators to develop effective strategies for long-term behaviour change.

